**LIST OF ABBREVIATIONS AND RELEVANT DEFINITIONS**

| **ADA** | **American Diabetes Association** |
| --- | --- |
| **AE** | **Adverse Event** |
| **AR** | **Adverse Reaction** |
| **CCMO** | **Central Committee on Research Involving Human Subjects; in Dutch: Centrale Commissie Mensgebonden Onderzoek** |
| **DCS** | **Decisional Conflict Scale** |
| **CV** | **Curriculum Vitae** |
| **EASD** | **European Association for the Study of Diabetes** |
| **EQ-5D** | **EuroQol – 5 dimension** |
| **EQ-VAS** | **EuroQol – visual analog scale** |
| **GLP-1** | **Glucagon-like peptide 1** |
| **GP** | **General Practitioner** |
| **HCP** | **Health Care Professionals** |
| **IC** | **Informed Consent** |
| **IPDAS** | **International Patient Decision Aids Standards** |
| **METC** | **Medical research ethics committee (MREC); in Dutch: medisch-ethische toetsingscommissie (METC)** |
| **NHG** | **Dutch College of General Practitioners; in Dutch: Nederlands Huisartsen Genootschap** |
| **PDA** | **Patient Decision Aid** |
| **PIF** | **Subject Information Sheet; in Dutch: patiënteninformatie** |
| **(S)AE** | **(Serious) Adverse Event** |
| **SDM** | **Shared decision-making** |
| **SGLT-2** | **Sodium-glucose contransport-2** |
| **Sponsor** | **The sponsor is the party that commissions the organisation or performance of the research, for example, a pharmaceutical**  **company, academic hospital, scientific organisation, or investigator. A party that provides funding for a study but does not commission it is not regarded as the sponsor but referred to as a subsidising party.** |
| **SUSAR** | **Suspected Unexpected Serious Adverse Reaction** |
| **T2DM** | **Type 2 Diabetes Mellitus** |
| **WMO** | **Medical Research Involving Human Subjects Act; in Dutch: Wet Medisch-wetenschappelijk Onderzoek met Mensen** |

**SUMMARY**

**Rationale:** Previous randomized controlled trials researching the effects of shared decision-making (SDM) support through patient decision aids (PDAs) for type 2 diabetes mellitus (T2DM) experienced several challenges related to study procedures, resources, and study management. These challenges include difficulties in recruiting participants, understandability of questionnaires, timely recruitment, and inadvertent recruitment bias. Small-scale piloting is crucial to address uncertainties around the feasibility of trial methods and to refine the study procedures of a large-scale economic evaluation. This protocol outlines a pilot study aimed at evaluating the feasibility of a future trial-based economic evaluation of a multistage SDM program, including a PDA for T2DM in the Netherlands. By conducting a pilot study, we aim to improve the quality of the intended trial-based economic evaluation.

**Objectives**: We will conduct a pilot study focused on the following questions to prepare for an intended economic evaluation of our multistage SDM program for T2DM: 1) How can we recruit and retain a representative sample of patients with T2DM in terms of sociodemographic and clinical background?; 2) How can we support primary care practices in managing the challenges associated with study participation?; 3) How can we feasibly measure relevant outcomes of SDM for T2DM using valid and reliable measurement instruments?

**Study design:** Our multistage SDM program will be piloted in a cluster-randomized controlled trial using a mixed-methods approach. Four primary care practices will be included, of which two will be randomly assigned to the intervention group and two to the control group.

**Study population:** Participants include adult patients with T2DM who need to decide on T2DM treatment based on the NHG guideline together with their primary care HCPs.

**Intervention**: Our multistage SDM program consists of 1) an online PDA; 2) preparatory consult to provide patients with the knowledge and confidence to participate in SDM; and 3) training to improve HCPs skills for SDM. Control practices will provide usual care.

**Main study parameters/endpoints:** The primary endpoints of the study are centered around the three objectives: 1) sample recruitment and retention (i.e. recruitment, retention, and consent rates, time required to target, and sociodemographic and clinical characteristics); 2) study management (time constraints and capacity issues); and 3) feasibility of outcome measurements (understandability and accessibility of measurement tools of the short- and long-term outcomes of the future economic evaluation).

**Nature and extent of the burden and risks associated with participation, benefit and group relatedness:** Participants will be asked to complete questionnaires. No medication interventions, treatments, or invasive procedures are involved, thereby minimizing physical strain and medical risks for the participants. We do not expect that there are any risks associated with completing the questionnaires. Moreover, the study requires limited involvement of patients and therefore imposes no burden.

1. INTRODUCTION AND RATIONALE

Diabetes mellitus is a highly prevalent disease that affects 10.5% of the world’s adult population, of which over 90% have type 2 diabetes mellitus (T2DM) [1]. T2DM is associated with significant levels of morbidity and mortality, reduced quality of life, and increased healthcare costs [2]. National and international clinical guidelines for T2DM emphasize the need for person-centered care, including shared decision-making (SDM), to decide on the best treatment course for an individual patient [3-5]. Care should be respectful of and responsive to individual patient preferences, needs and values, and ensure that these guide clinical decisions [6]. However, with many pharmacological and lifestyle treatment options available, SDM is complex in T2DM care. Patients and healthcare professionals (HCPs) face difficult trade-offs in aligning treatment attributes (e.g. efficacy, side effects) with patients’ clinical factors and preferences. SDM support is needed to reap the full benefits of person-centered T2DM care.

In general, patient decision aids (PDAs) are a type of SDM support that aims to help patients and HCPs make informed decisions [2]. PDAs include information about the treatment options that require consideration, along with their associated risks and benefits. Evidence shows that PDAs can reduce patients’ decisional conflict, make them better informed, more involved, and satisfied with their treatment choices, and have a positive effect on the communication between patients and HCPs [7]. There is some evidence suggesting that PDAs, through their effective support of SDM, can lead to improvements in treatment adherence and persistence, thereby resulting in better health outcomes and cost reduction [7]. However, the available evidence for these effects remains limited [7]. While the potential benefits of using PDAs in healthcare are promising, research shows that only 44% of PDAs are used in practice following their trial [8]. This highlights the need for implementation research for PDAs. Economic evaluation strengthens the limited evidence about the impact of person-centered care and SDM on mid and long-term outcomes such as treatment adherence, health outcomes, and costs [7].

Previous randomized controlled trials researching the effects of SDM support through PDAs for T2DM experienced several challenges related to study procedures (i.e. recruitment, understandability of questionnaires), resources (i.e. time and resource problems), and study management (i.e. human and data management problems) [9-12]. These challenges include, for example, difficulties in recruiting participants, understandability of questionnaires, timely recruitment, and inadvertent recruitment bias. Recognizing the challenges faced in previous research, small-scale piloting is crucial to address uncertainties around the feasibility of trial methods and to refine the study procedures of a large-scale economic evaluation [13, 14]. This research protocol outlines the protocol for a pilot study aimed at evaluating the feasibility of a future trial-based economic evaluation of a multistage SDM program, including a PDA for T2DM in the Netherlands, compared to usual care [15]. By conducting a pilot study, we aim to improve the quality of the intended trial-based economic evaluation. The pilot study specifically focuses on sample recruitment and retention, study management, and feasibility of outcome measurement, aiming to identify and address potential challenges in the intended large-scale economic evaluation. The reasoning for why we specifically focus on these three topics is described below.

Given that T2DM affects a large and diverse group of patients, it is important to ensure that the study participants accurately represent this diversity, as it is essential for our intended economic evaluation [16]. Previous randomized controlled trials researching the effects of PDAs for T2DM experienced recruitment challenges [9-12]. These trials reported difficulties in recruiting sufficient participants, timely recruitment, and inadvertent recruitment bias. Moreover, some trials were unable to include a representative sample of patients with T2DM [10, 12]. We will therefore place a strong emphasis on the feasibility of the study processes in terms of recruitment, retention, and consent rates within the pilot study. This will improve our understanding and we can apply these insights to the recruitment process of the intended economic evaluation.

HCPs in primary care practices are faced with a high workload, time constraints, and stress which are also identified as barriers to research participation [17-19]. To avoid willingness and capacity problems of the participating practices related to the study, it is important to limit time expenses and paperwork, and to provide adequate information and support. Therefore, as part of the pilot study, we focus on how we can support general practices in effectively managing the challenges associated with study participation. These insights will be instrumental in ensuring the successful implementation of the multistage program into routine practice while minimizing the additional burden on practices.

There are valid and reliable instruments available for the primary and secondary outcomes of the intended trial-based economic evaluation. The measurement process can be complex since outcomes are collected using different methods, from different sources, and at various time points. It is important to avoid data management problems and ensure successful data triangulation in the large-scale study. Hence, the primary and secondary outcomes will be measured and analyzed during the small-scale pilot study. In the pilot study, we also focus on the understandability and accessibility of the measurement tools and possible improvements thereof. This is especially important since approximately 24.5% of the Dutch population experience low health literacy and may therefore face difficulties when completing questionnaires [20]. Overall, the insights gained from the pilot study will guide the refinement of the study procedures and intervention components for the intended economic evaluation.

1. OBJECTIVES

Primary Objective:

Small-scale piloting is crucial to address uncertainties around the feasibility of trial procedures, resources, and study management [13, 14]. Our pilot aims to improve the conduct and quality of an intended trial-based economic evaluation of our multistage SDM program for T2DM. The pilot study will specifically focus on strategies to deal with recruitment and retention challenges and gain insights into how to minimize additional burdens on participating primary care practices. Moreover, the outcomes of the intended large-scale economic evaluation will be measured to identify possible data management issues and subsequently refine study procedures. We will conduct a pilot study focused on the following questions to prepare for an intended economic evaluation of our multistage SDM program for T2DM:

1. How can we recruit and retain a representative sample of patients with T2DM in terms of sociodemographic and clinical background?
2. How can we support primary care practices in managing the challenges associated with study participation?
3. How can we feasibly measure relevant outcomes of SDM for T2DM using valid and reliable measurement instruments?
4. STUDY DESIGN

This protocol follows the Standard Protocol Items: Recommendations for Interventional Trials (SPIRIT) 2013 statement and guidelines [21, 22], and the Consolidated Health Economic Evaluation Reporting Standards 2022 (CHEERS 2022) Statement [23] (attached to the protocol as separate documents). The Dutch guidelines for economic evaluation will also be followed [24].

*Study design*

Our multistage SDM program will be piloted in a cluster-randomized controlled trial using a mixed-methods approach to answer questions related to sample recruitment and retention, study management, and feasibility of outcome measurements. Four primary care practices will be included in this pilot study. Randomization will be conducted by cluster (i.e. primary care practices) to avoid possible contamination between the intervention and control group [25]. Two primary care practices will be randomly assigned to the intervention group and two to the control group. Simple randomization will be used to assign each primary care practice to a group with an equal probability (1:1 allocation) using a computerized random number generator [26]. Given the nature of the intervention, both patients with T2DM and HCPs are not blinded to the group assigned to them. The intervention practices will have access to the multistage SDM program. Patients and HCPs in the control practices will provide and receive usual care according to the national guidelines for T2DM of the Dutch College of General Practitioners (NHG) [5]. They will not have access to the multistage program. Data will be collected from patients with T2DM and healthcare professionals from both the intervention and control practices.

*Study duration*

The study will last 18 months: 3 months for study preparation, 9 months for implementation (i.e. patient recruitment and data collection) of the SDM program, and 6 months for data analysis and reporting.

*Study setting*

The majority of patients with T2DM in the Netherlands (90% in 2022) are treated in a primary care setting organized by care groups [27]. Care groups are collaborations between healthcare professionals (general practitioners and affiliated personnel) and are responsible for organizing, coordinating, and providing care for patients with T2DM in their region [28]. A team comprising a general practitioner and practice/diabetes nurse provides treatment following the national guidelines for T2DM of the NHG. The national guidelines underwent significant revisions in 2018 and 2021 allowing the use of new pharmacological agents (e.g., sodium-glucose cotransport 2 [SGLT2] inhibitors and glucagon-like peptide 1 [GLP-1] receptor agonists) for high-risk patients [5]. Patients are considered high risk if they have, amongst others, a history of cardiovascular disease or heart failure. The SGLT2 inhibitors and GLP-1 receptor agonists are also included in the treatment guidelines of the American Diabetes Association (ADA) and the European Association for the Study of Diabetes (EASD) [4]. Since most Dutch patients with T2DM are treated in primary care, the multistage SDM program was developed based on the NHG guideline for T2DM and will be pilot-tested in a general practice setting.

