| Health-related quality of life | Patient | Dutch EuroQol (EQ) 5D-5L (quality of life) | The EQ 5D-5L assesses quality of life and includes the EQ-5D dimension and the EQ visual analog scale (VAS). EQ-5D comprises five dimensions: mobility, self-care, usual activities, pain, and anxiety. Each dimension of the EQ-5D is scored on a five-point Likert score (from no problems to extreme problems). The EQ VAS is used to assess the patient’s self-reported health on a visual analog scale. |

*Timeline*

The schedule of study enrolment and assessment can be found in Table 2. There are some differences in the timeline between participating patients in the intervention practices and control practices.

- - - - Intervention practices

Baseline measurements will capture sociodemographic and clinical patient characteristics, patient knowledge, glycemic control, medication adherence, costs, and health-related quality of life. Patients complete the DCS, CollaboRATE survey, and SDM-Q-9 questionnaire directly following the clinical encounter where a treatment decision is made.

- - - - Control practices

Patients will complete all questionnaires (sociodemographic and clinical characteristics, patient knowledge, glycemic control, medication adherence, costs, and health-related quality of life) directly following the clinical encounter where a treatment decision is made.

For both study arms, HCPs complete the SDM-Q-Doc questionnaire directly following the clinical encounter where a treatment decision is made. Follow-ups at 3 months and 9 months will facilitate the measurement of glycemic control, medication adherence, costs, and health-related quality of life. Semi-structured interviews with patients will be held within 1 month after study participation and the focus groups with HCPs from participating practices will be held at the end of the 9 months of implementation.

**Table 1.** Schedule of study enrolment and assessment.

|  |  | Enrolment |  |  |  |  |
| --- | --- | --- | --- | --- | --- | --- |
| Time point |  |  | t0 | t1 | t2 | t3 |
| Enrolment | Eligibility | x |  |  |  |  |
|  | Informed consent | x |  |  |  |  |
| Patient assessment (intervention) | Sociodemographic and clinical characteristics |  | x |  |  |  |
|  | Decisional Conflict |  |  | x | x | x |
|  | Patient-rated level of SDM |  |  | x | x | x |
|  | Patient knowledge |  | x |  |  |  |
|  | Medication adherence |  | x |  | x | x |
|  | Glycemic control |  | x |  | x | x |

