|  | Costs |  | x |  | x | x |
|  | Health-related quality of life |  | x |  | x | x |
|  | Semi-structured interviews with patients |  |  | x |  |  |
| Patient assessment (control) | Sociodemographic and clinical characteristics |  |  | x |  |  |
|  | Decisional Conflict |  |  | x | x | x |
|  | Patient-rated level of SDM |  |  | x | x | x |
|  | Patient knowledge |  |  | x |  |  |
|  | Medication adherence |  |  | x | x | x |
|  | Glycemic control |  |  | x | x | x |
|  | Costs |  |  | x | x | x |
|  | Health-related quality of life |  |  | x | x | x |
|  | Semi-structured interviews with patients |  |  | x |  |  |
| HCP assessment | HCP-level of SDM |  |  | x |  |  |
|  | Focus group with HCPs |  |  |  |  | x |

t0 = baseline measurement; t1 = directly following the clinical encounter where a treatment decision is made; t2 = 3-month follow-up; t3 = 9-month follow-up. SDM: shared decision-making, HCP: healthcare professional.

All questionnaires (added as separate documents to the research protocol) will be included in the digital platform of PatientPlus. Participating patients and HCPs from the intervention practices will have an account giving them access to the PatientPlus platform. Patients and HCPs from the intervention practices are asked to complete the questionnaires via the online platform of PatientPlus. After 3 and 9 months, the patient will receive automatic notifications (via mail) prompting them to complete the follow-up questionnaires. Additionally, automated reminders will be sent if the patient has not yet completed the questionnaire.

Patients and HCPs from the control group will not have an account on the PatientPlus platform to avoid bias. They will complete questionnaires via Qualtrics [45]. After 3 and 9 months, the patient will receive automatic notifications (via mail) prompting them to complete the follow-up questionnaires. Additionally, automated reminders will be sent if the patient has not yet completed the questionnaire.

- 1. Withdrawal of individual subjects

Subjects can leave the study at any time for any reason if they wish to do so without any consequences. The investigator can decide to withdraw a subject from the study for urgent medical reasons.

- - 1. Specific criteria for withdrawal (if applicable)

Not applicable.

- 1. Replacement of individual subjects after withdrawal

Not applicable.

- 1. Follow-up of subjects withdrawn from treatment

Not applicable.

- 1. Premature termination of the study

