We request that patients fill out questionnaires at three (control group) or four (intervention group) time points spanning 9 months: at the onset of participation, after 3 months, and at 9 months. These questionnaires are accessible through the PatientPlus online platform or Qualtrics (depending on whether the patient/HCP is in the intervention or control group). For the intervention group, the initial questionnaire comprises two parts, with part 1 being completed after signing the informed consent, taking approximately 5-10 minutes. Subsequently, upon making a treatment decision for type 2 diabetes with their healthcare provider, patients proceed to complete part 2, which requires around 15-25 minutes. Patients in the control group will complete part 1 and part 2 of the questionnaires at the same time (i.e. after the consult where a treatment decision was made). Automated reminders prompt patients to complete subsequent questionnaires after 3 and 9 months, each requiring approximately 5-10 minutes for completion.

Patient questionnaire responses will remain confidential and inaccessible to healthcare providers, ensuring the privacy of the patients. The interviews are optional for patients. When signing the informed consent, they have the option to indicate whether they grant permission for researchers to contact them for an interview. During the interviews, participants will be asked about the readability and understandability of the questionnaires. Thus, the study does not affect the mental integrity of the participants. Moreover, the study requires limited involvement of patients and therefore imposes no burden.

In summary, participating patients will have the opportunity to contribute to advancements in the field of person-centered care for the treatment of T2DM. The careful design of the study ensures the safety and well-being of the participants. The scientific and societal benefits of their involvement underscore the importance of this research in advancing the understanding and practice of person-centred care in the context of T2DM.

- 1. Compensation for injury

The sponsor has a liability insurance which is in accordance with article 7 of the WMO.

The sponsor (also) has an insurance which is in accordance with the legal requirements in the Netherlands (Article 7 WMO). This insurance provides cover for damage to research subjects through injury or death caused by the study.

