Documentation of the data will be done to keep data usable and understandable. The data documentation will include information about the context of the data collection, collection methods, data manipulations, different versions, etc. A folder structure will be defined before the start of the data collection.

A data management plan was drawn and approved by the data steward of the sponsor. The data management plan is attached to the protocol as a separate document. The plan encompasses key elements such as data processing and data archiving.

- 1. Monitoring and Quality Assurance

Not applicable.

- 1. Amendments

Amendments are changes made to the research after a favourable opinion by the accredited METC has been given. All amendments will be notified to the METC that gave a favourable opinion.

- 1. Annual progress report

The investigator will submit a summary of the progress of the trial to the accredited METC once a year. Information will be provided on the date of inclusion of the first subject, numbers of subjects included and numbers of subjects that have completed the trial, serious adverse events/ serious adverse reactions, other problems, and amendments.

- 1. Temporary halt and (prematurely) end of study report

The investigator will notify the accredited METC of the end of the study within a period of 8 weeks. The end of the study is defined as the completion of the questionnaires at 9-month follow-up of the last patient.

The sponsor will notify the METC immediately of a temporary halt of the study, including the reason of such an action.

In case the study is ended prematurely, the sponsor will notify the accredited METC within 15 days, including the reasons for the premature termination.

Within one year after the end of the study, the investigator/sponsor will submit a final study report with the results of the study, including any publications/abstracts of the study, to the accredited METC.

- 1. Public disclosure and publication policy

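### The 3 + 9 + 6 month calendar puts recruitment and data collection in one 9-month period, which does not reconcile with a 9-month follow-up for every patient

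*Protocol*

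**What the plan says.** **Calendar.** Under Study duration in the Study Design section, the protocol says "The study will last 18 months: 3 months for study preparation", then "9 months for implementation (i.e. patient recruitment and data collection) of the SDM program", then "6 months for data analysis and reporting". Recruitment is given no period of its own.

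**Follow-up.** Section 8.3 (Timeline) says "Follow-ups at 3 months and 9 months will facilitate the measurement of glycemic control, medication adherence, costs, and health-related quality of life", for both arms. The footnote to the assessment schedule defines "t2 = 3-month follow-up; t3 = 9-month follow-up". Section 11.4 describes questionnaires at "time points spanning 9 months: at the onset of participation, after 3 months, and at 9 months". Section 8.3 also has automatic prompts and reminders going to patients in both arms at 3 and 9 months.

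**Focus groups.** Section 8.3 states that "the focus groups with HCPs from participating practices will be held at the end of the 9 months of implementation". The schedule marks them at t3.

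**End of study.** Section 12.5 states: "The end of the study is defined as the completion of the questionnaires at 9-month follow-up of the last patient".

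**Endpoints affected.** Section 8.1.1 lists retention and the time taken to reach the recruitment target among the primary feasibility endpoints. It also asks whether adherence, HbA1c, costs and quality of life can feasibly be measured. Section 4.4 raises the sample from 30 to 40 to allow for loss to follow-up.

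**The concern.** A 9-month period that holds both recruitment and data collection leaves no time for recruitment if each patient is followed for 9 months. Enrolling all 40 patients on the first day is not a realistic way out. Eligible patients must currently face a treatment decision, so they will present over time, and the introduction gives difficulty with timely recruitment in earlier trials as a reason for the pilot.

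The focus-group wording points to the same slip. The end of implementation and t3 are treated as one moment, which is true only for a patient enrolled on day one.

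What is at stake is the interpretation of a primary endpoint. If a site or data manager takes the 9-month period as the collection window, t3 will be missing for administrative reasons. A retention rate computed on all enrolled patients would then look like dropout and would misinform planning of the main trial. If follow-up instead runs to its natural end, the time shown for analysis is not available as stated.

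**Working it through.** **Inputs from the protocol:** preparation 3 months, implementation 9, analysis and reporting 6 (Study Design); follow-up at 3 and 9 months (sections 8.3 and 11.4); 40 patients (section 4.4).

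**Assumptions, because the protocol is silent:** recruitment lasts R months, with R from 1 to 9; accrual is even; follow-up is counted from enrolment.

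**Step 1. Stated total.** 3 + 9 + 6 = 18 months. The protocol's figure reproduces.

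**Step 2. Latest enrolment that reaches follow-up F inside the 9-month period.** This is 9 - F.
- t3: 9 - 9 = month 0.
- t2: 9 - 3 = month 6.

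**Step 3. Share reaching each visit inside the period.**
- t3: max(0, min(R, 9 - 9)) / R = 0 for every R above zero, so 0 of 40.
- t2: min(R, 6) / R. This is 40 of 40 if R is at most 6. If R = 9 it is 6/9 = 67%, about 27 of 40.

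**Step 4. Calendar if every patient is followed to t3.**
- Last t3 at study month 3 + R + 9 = 12 + R.
- Analysis time left within 18 months: 18 - (12 + R) = 6 - R.
- Total if all 6 analysis months follow the last t3: 3 + R + 9 + 6 = 18 + R.

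| R (months, assumed) | Last t3 (study month) | Analysis left within 18 months | Total if 6 analysis months are kept |
|---|---|---|---|
| 1 | 13 | 5 | 19 |
| 3 | 15 | 3 | 21 |
| 6 | 18 | 0 | 24 |
| 9 | 21 | 3 short | 27 |

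**Step 5. Collection allowed to run to month 18.** The share reaching t3 by then is min(R, 6) / R. That is 40 of 40 if R is at most 6, and 6/9 or about 27 of 40 if R = 9.

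No value of R above zero satisfies the 3/9/6 split and the 9-month follow-up together.

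**The case against.** The strongest reply is that the duration paragraph is a planning sentence, not a data cut-off. Section 12.5 keeps the study open until the last patient's 9-month questionnaire, section 8.3 sends 9-month prompts to patients in both arms, and nothing says collection stops at study month 12 or that late enrolees are cut short. This reply stands in part, and it limits the point in several ways.

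- A reader might infer that 9-month retention cannot be observed at all. The protocol does not support that. It plainly intends to collect t3 for everyone, and the 0 of 40 result applies only if the 9-month period is enforced as the collection window.
- A reader might infer that the 18-month total must be wrong. It need not be. With R of at most 6 months the last t3 falls by month 18. The analysis is descriptive (section 10.1), so part of it could overlap with follow-up, and section 12.5 allows a year after the end of study for the final report. What fails is the split.
- A reader might infer that time to target is compromised as well. It is observed however follow-up is scheduled.
- A reader might count t3 from the treatment-decision encounter, which would enlarge the shortfall in the intervention arm. The protocol does not fix that anchor, and section 11.4 suggests counting from the onset of participation.
- Moving the focus groups to the end of recruitment would be a preference. They also cover study management and the clinicians' questionnaire.

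The reply does not remove the contradiction. Relying on section 12.5 concedes that the calendar in the Study Design section cannot be carried out as written.

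**Conclusion.** The concern holds as an internal inconsistency: the stated calendar does not reconcile with the follow-up schedule or with the end-of-study definition. The size depends on which text governs.

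- If the 9-month period is the collection window, only a patient enrolled on its first day can reach t3 inside it, and apparent retention would be an artefact.
- If the end-of-study definition governs, no t3 need be lost, but the last one falls between study months 13 and 21. Within 18 months, that leaves between 5 months for analysis and a 3-month overrun.

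These ranges rest on the assumed R of 1 to 9 months and on counting from enrolment. The t2 share and the share reaching t3 by month 18 also assume even accrual. The impossibility of the split needs none of these beyond R above zero. The sample size calculation is unaffected. The calendar should be corrected before recruitment is planned around it.

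**What to change.** Amend the duration paragraph to give a recruitment window R, followed by follow-up until the last patient reaches 9 months. Then choose one of two options:

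1. Keep 18 months in total, with R at most 6, and state that only 6 - R months remain for analysis after the last t3. For example: 3 preparation + 3 recruitment + 9 follow-up + 3 analysis = 18.
2. Keep 6 months of analysis after the last t3 and restate the total as 18 + R months.

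Reconcile the focus-group timing in section 8.3 and in the schedule with the revised calendar, since the end of implementation and t3 will no longer coincide. If any administrative cut-off is applied before the last t3, compute t3 retention only among patients whose 9 months have elapsed by then. Without such a cut-off, that rule is not needed.

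The cost is a text amendment with no extra patients or procedures. The real price is a shorter recruitment or analysis window under the first option, or a longer stated duration under the second.
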